## Abstract

**Background:**

The acknowledgment of the mental health toll of the COVID-19 epidemic in healthcare workers has increased considerably as the disease evolved into a pandemic status. Indeed, high prevalence rates of depression, sleep disorders, and post-traumatic stress disorder (PTSD) have been reported in Chinese healthcare workers during the epidemic peak. Symptoms of psychological distress are expected to be long-lasting and have a systemic impact on healthcare systems, warranting the need for evidence-based psychological treatments aiming at relieving immediate stress and preventing the onset of psychological disorders in this population. In the current COVID-19 context, internet-based interventions have the potential to circumvent the pitfalls of face-to-face formats and provide the flexibility required to facilitate accessibility to healthcare workers. Online cognitive behavioral therapy (CBT) in particular has proved to be effective in treating and preventing a number of stress-related disorders in populations other than healthcare workers. The aim of our randomized controlled trial study protocol is to evaluate the efficacy of the ‘My Health too’ CBT program—a program we have developed for healthcare workers facing the pandemic—on immediate perceived stress and on the emergence of psychiatric disorders at 3- and 6-month follow-up compared to an active control group (i.e., bibliotherapy).

**Methods:**

Powered for superiority testing, this six-site open trial involves the random assignment of 120 healthcare workers with stress levels > 16 on the Perceived Stress Scale (PSS-10) to either the 7-session online CBT program or bibliotherapy. The primary outcome is the decrease of PSS-10 scores at 8 weeks. Secondary outcomes include depression, insomnia, and PTSD symptoms; self-reported resilience and rumination; and credibility and satisfaction. Assessments are scheduled at pretreatment, mid-treatment (at 4 weeks), end of active treatment (at 8 weeks), and at 3-month and 6-month follow-up.

**Discussion:**

This is the first study assessing the efficacy and the acceptability of a brief online CBT program specifically developed for healthcare workers. Given the potential short- and long-term consequences of the COVID-19 pandemic on healthcare workers’ mental health, but also on healthcare systems, our findings can significantly impact clinical practice and management of the ongoing, and probably long-lasting, health crisis.

**Trial registration:**

ClinicalTrials.gov NCT04362358, registered on April 24, 2020.

## Background

The acknowledgment of the mental health toll of the COVID-19 epidemic both in the general population [1–5] and in healthcare workers [6–11] has increased dramatically in the last few weeks as the disease has grown into a pandemic status.

Indeed, preliminary epidemiological and qualitative findings suggest that the epidemic might have negative immediate as well as long-term mental health effects, particularly in healthcare workers [12]. For instance, in one of the first reports published by a Chinese team, frontline healthcare workers were found to present with extremely high rates of depression (> 50%), generalized anxiety disorder (> 44%), insomnia (> 36%), and stress-related symptoms (> 73%) [13]. Since then, numerous studies have further confirmed these findings in nurses [11, 14], physicians and medical staff [6, 8, 12, 15], and trainees [10, 16] and warranted the need for psychological treatments aiming at relieving immediate stress and preventing the onset of psychological disorders in healthcare workers [12]. To address this need, we developed a 7-session online cognitive behavioral therapy (CBT) program targeting the reduction of stress and the reinforcement of adaptive coping behaviors in healthcare workers during the COVID-19 pandemic. The aim of our randomized controlled trial study protocol is to evaluate the efficacy of the treatment we have designed for healthcare workers—the ‘My Health too’ CBT program—on immediate perceived stress, as well as on the emergence of psychiatric disorders at 3- and 6-month follow-up (Fig. 1).

**Fig. 1 Fig1:**
[figure not shown]
Flow chart of the REST study

While the long-term mental health effects of the COVID-19 pandemic are still unknown, studies conducted following the SARS-CoV-1 outbreak in 2003 suggest that healthcare workers are particularly at risk of developing severe mental health disorders following the acute stages of the current pandemic [17, 18]. For instance, healthcare workers in hospitals in Toronto who treated SARS-CoV-1 patients continued to show symptoms of severe psychological distress 1 and 2 years post-outbreak [19, 20], with 13.8% presenting with significant symptoms of posttraumatic stress disorder (PTSD) [17]. Irrespective of the contamination status, fewer years of experience and personal history of psychiatric disorder were among the main predisposing factors involved in the emergence of psychiatric disorders [20]. In addition to effects on their individual well-being, there was also a long-term systemic impact of these mental health problems, as healthcare workers reported reduced patient contact and hours of healthcare work as well as more frequent sick absences and increased behaviors that could affect their work [19]. It is noteworthy that although the lethality of the SARS-CoV-2 is lower than that associated with the SARS-CoV-1, the SARS-CoV-2 is more contagious, and the COVID-19 has become much more widespread [14]. Hence, it is possible that the mental health impact of the current pandemic on healthcare workers, as well as its systemic impacts, will be equally or even more long-lasting and severe than those reported following the SARS-CoV-1 outbreak [12, 17].

A number of solutions were implemented in China to prevent psychiatric disorders in healthcare workers, such as telephone hotlines and face-to-face group or individual psychotherapy sessions [21]. However, healthcare workers’ use of these interventions was limited, probably due to workload as well as fear of contamination [21]. In this context, web-based programs represent a more feasible format, because of their high dissemination potential and flexibility. Indeed, such programs can be made available to a high number of people, who have variable schedules, an important workload, and who are afraid of being contaminated themselves in face-to-face intervention formats [13] (Table 1).

**Table 1 Tab1:**
[figure not shown]
Schedule for the REST study

**PSS-10* Perceived Stress Scale, *PHQ-2* Patient Health Questionnaire, *SF-PCL-5* Posttraumatic stress disorder CheckList scale Short Form, *CD-RISC 2* Connor-Davidson Resilience Scale, *SF-ISI* Insomnia Severity Index Short Form, *VAS* visual analogic scale, *CEQ* Credibility Expectancy Questionnaire, *CSQ-8* Client Satisfaction Questionnaire

^a^Assessed in experimental group before each session

^b^Assessed in experimental group after each session

CBT has been found to be effective in the prevention of burnout in healthcare workers, in stressful contexts other than the current COVID-19 pandemic [22]. Moreover, there is evidence of the effectiveness of CBT in the prevention of a number of psychiatric disorders in at-risk individuals, such as PTSD [23] and depression [24]. Despite a growing interest in the field of web-based psychological interventions, internet-based CBT remains under-developed [24, 25], and, to our knowledge, internet-based CBT programs specifically designed to address stress-related conditions in healthcare workers are lacking [26].

Given its demonstrated efficacy and feasibility in the treatment of stress and in the cultivation of resilience in other populations (e.g., college students and firefighters) [25, 27, 28], it is crucial to fill this important gap in the research through the investigation of the efficacy of internet-based CBT programs targeting stress and resilience in healthcare workers. This is all the more urgent in the current pandemic context, which requires a number of unplanned adaptations of psychological interventions in order to address the psychological needs of patients [7], i.e., social distancing measures, working under extraordinary stressful circumstances, increased workload, and variable work schedules [21].

The aim of the present randomized controlled trial is to investigate the efficacy and the acceptability of a 7-session internet-based CBT program we have developed to address the immediate stress and prevent its long-term consequences, in healthcare workers during the COVID-19 pandemic. To assess its impact on perceived stress, we will compare the effects of the internet-based ‘My Health too’ 7-session CBT intervention to that of bibliotherapy on self-reported measures of perceived stress immediately following the 8-week intervention as well as at 3- and 6-months follow-up. We chose bibliotherapy as an active control comparison group because it offers participants unguided access to online self-help stress-reduction material, akin to ecological self-help situations, that should nevertheless be less efficacious than online CBT [29]. In both arms, human support is available to all participants included in the trial via their optional use of the COVID-19 psychological hotlines. Subjects will be randomly allocated, following a 1:1 ratio with stratification by site, either to the online CBT group or the bibliotherapy group. We expect scores on the 10-item Perceived Stress Scale [30] to be significantly decreased in the online CBT group compared to the bibliotherapy group over the course of the 8-week period of treatment. Moreover, participants in the online CBT group should present with decreased symptoms of PTSD, insomnia, and depression compared to the bibliotherapy group both immediately following the 8-week treatment period, but also at 3- and 6-month follow-up. In order to evaluate acceptability, we will assess attrition rates, client satisfaction, and therapy credibility. Finally, we were also interested in the psychological and contextual dimensions (e.g., medication, sleep quality, perceived resilience, rumination, post-traumatic, and depressive symptoms) that might mediate the efficacy of online CBT as well as the demographic, occupational, and medical data (e.g., experience on the job and psychiatric history) that might predict efficacy. This is crucial in order to improve treatment effectiveness in the future and the prevention of psychological disorders in healthcare workers.

## Methods/design

### Design

Our project consists of a six-site, prospective, randomized, open and parallel group-controlled study with two arms: an experimental arm with 7 online CBT sessions and an active control arm consisting of online bibliotherapy. In addition to these interventions, each participant enrolled in the study will be informed that they can make use of the psychological hotline via the website throughout the 8-week treatment duration, in case they need to have access to a qualified therapist. The study was approved by the relevant local ethics committee (Comité de Protection des Personnes Ile-de-France VI, May 7, 2020, N 36-20) and registered at ClinicalTrials.gov on 24 March 2020 (study identifier NCT04362358).

### Study population

Participants will meet the following inclusion criteria: (1) belong to one of the following professions: medical doctors, nurses, orderlies, physiotherapists, psychologists, hospital porters, ambulance drivers, nursing and medical students working in hospitals; (2) aged 18–70 years old; and (3) fluent in the French language. Exclusion criteria include (1) initial score at the Perceived Stress Scale-10 (PSS-10) [30]< 16 (which means that the participant has a non-significant level of stress), (2) suicidal ideation score assessed by the question 9 of the Patient Health Questionnaire - 9 (PHQ-9) [31] > 2, and (3) be under guardianship. Participants will be recruited by psychiatrists or psychologists in six hospitals of the East region of France, i.e., Hôpitaux Universitaires de Strasbourg, Hôpitaux Civils de Colmar, Groupe Hospitalier Régional de Mulhouse Sud-Alsace, Centre Hospitalier Universitaire de Nancy, Centre Hospitalier Universitaire de Besançon, and Centre Hospitalier Universitaire de Dijon; the East region was the region that was the most affected by the COVID-19 in France. Demographic information (gender, age, family situation), medical history, and occupational exposure (i.e., position, service, seniority on the job, working time, COVID-19 infection status) will be collected.

### Trial status

This is the first version of the protocol (May 7, 2020). Study enrollment has not started yet and will begin in June 2020. The active treatment phase is expected to be finished in September 2020. The completion of follow-up assessments is expected in November 2020 and February 2021. The total sample of 120 participants will be completed by February 2021.

### Sample size

The number of subjects required was calculated based on the data from Rose et al. [25] which showed a relative decrease in the PSS-10 score of 15% in the control group and 30% in the experimental group. Mean score values with a standard deviation (< 5) were reported. Given that the healthcare professionals recruited in our study will be under greater stressors than Rose et al.’s [25] study sample, which consisted of college students, the expected values of PSS-10 at baseline are 23 ± 5 with a decrease to 19.6 ± 5 in the control group and 16 ± 5 in the experimental group. Simulations using a mixed linear regression model showed that 46 subjects per group, i.e., 92 in total, would be needed to highlight a difference between groups with a power of more than 90% and an alpha risk set at 5%. Considering an estimation of 10% of exclusions (initial PSS-10 < 16) and 20% of drop-outs, the number of subjects in the study was increased to 120 subjects in total (Fig. 1).

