Their active participation in the program will last 8 weeks. Throughout the 8-week duration of the program, each participant (either in the experimental or the control condition) will have access to the psychological hotline (from Monday to Friday between 9 a.m. and 5 p.m.), if they need support in using the resources made available to them. We chose to provide supported interventions instead of fully automated, stand-alone internet-based CBT and bibliotherapy, as the latter generally have higher treatment dropout rates (74%) than those provided with therapist or administrative support (28% and 38%, respectively) [41]. Moreover, in the context of the current pandemic and its social distancing-related guidelines, actual social support has been highlighted as particularly necessary in order to improve well-being [42]. During the study, participants are allowed to benefit from any medical or psychological follow-up or to take psychotropic drugs when prescribed by a medical doctor.

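### The target of 120 adds the expected losses to 92 instead of dividing by retention, and the article contradicts itself on whom the 120 counts and on the PSS-10 entry cut-off

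*Protocol article*

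**What the plan says.** Under Sample size, the expected PSS-10 values are "23 ± 5 with a decrease to 19.6 ± 5 in the control group and 16 ± 5 in the experimental group". From simulations with a mixed linear model, "46 subjects per group, i.e., 92 in total, would be needed to highlight a difference between groups"; the claimed power is above 90%, at an alpha of 5%. The section then inflates this number, first for people who do not meet the stress criterion: "Considering an estimation of 10% of exclusions (initial PSS-10 < 16"). Attrition comes next, together with the resulting target: "20% of drop-outs, the number of subjects in the study was increased to 120 subjects in total". No inflation formula is shown.

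The Abstract (Methods) describes the same number differently, as the "random assignment of 120 healthcare workers with stress levels" above 16 on the PSS-10. Study population and Sample size instead treat a PSS-10 below 16 as the exclusion.

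Under Procedure, the choice of supported formats is justified by lower treatment drop-out: stand-alone programmes have higher rates (74%) "than those provided with therapist or administrative support (28% and 38%, respectively").

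**The concern.** Three stated items do not fit together.

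- **Inflation.** Percentages that describe losses from the enrolled sample seem to have been applied to the evaluable number. That always gives too small a target.
- **Denominator.** If all 120 are randomised after meeting the stress criterion, none can later be lost to that criterion. If 10% can be lost to it, 120 is either a count taken before eligibility is settled or it includes exclusions after randomisation. The second would sit badly with the intention-to-treat analysis under Statistical analyses.
- **Cut-off.** Someone scoring exactly 16 is outside the population in the Abstract and inside it under Study population.

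In addition, the assumed 20% drop-out lies below both rates that the article cites for supported programmes.

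At stake are the evaluable number, the power statement, and whether sites recruit to a screening target or a randomisation target.

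**Working it through.** **Inputs.** From Sample size: 46 per arm (92 in total), week 8 means 19.6 and 16, SD 5, alpha 5%, power above 90%, exclusions 10%, drop-out 20%, total 120. From Procedure: treatment drop-out of 28% and 38%. Assumed: a two-sided test, and a baseline to week 8 correlation ρ, which the article does not give.

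**1. Reproducing 120.**
- Adding: 92 × (1 + 0.10 + 0.20) = 119.6, which rounds to 120.
- Compounding upwards: 92 × 1.1 × 1.2 = 121.4, close but not 120.
- Dividing by retention for both losses: 92/(0.9 × 0.8) = 127.8, so 128.
- Dividing by the summed losses: 92/0.7 = 131.4, so 132.
- Dividing for drop-out alone: 92/0.8 = 115.

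Only the additive route gives 120.

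**2. What 120 leaves.**
- Both stated losses fall on the 120: 120 × 0.9 × 0.8 = 86.4, about 43 per arm.
- All 120 are eligible and randomised, 20% drop-out: 120 × 0.8 = 96, 48 per arm.
- All eligible, 28% loss: 120 × 0.72 = 86.4, about 43 per arm.
- All eligible, 38% loss: 120 × 0.62 = 74.4, about 37 per arm.

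**3. Power.** The test of interest is the group-by-time interaction over baseline and week 8, that is, the difference in change. The SD of change is 5 × √(2(1 − ρ)), which is 5.0 at ρ = 0.5. Power is from the noncentral t with noncentrality Δ/(SD × √(2/n)), where n is the number per arm.

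The plan's own claim bounds ρ: with Δ = 19.6 − 16 = 3.6 and 46 per arm, power reaches 90% only if ρ is about 0.44 or more.

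| n per arm | Δ 3.6, ρ ≈ 0.44 | Δ 3.6, ρ 0.5 | Δ 3.6, ρ 0.6 | Δ 3.45, ρ 0.5 |
|---|---|---|---|---|
| 48 | 91% | 93.7% | 97.4% | 91.7% |
| 46 | 90% | 92.7% | 96.8% | 90.6% |
| 43 | 88% | 91.0% | 95.8% | 88.5% |
| 37 | 83% | 86.3% | 92.7% | 83.3% |

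At 43 per arm, power falls below 90% only if ρ is below about 0.48.

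**4. The difference of 3.45.** The source study "showed a relative decrease in the PSS-10 score of 15% in the control group and 30% in the experimental group". Applied to 23, this gives 23 × 0.85 = 19.55 and 23 × 0.70 = 16.10, a difference of 3.45 against the 3.6 used. The last table column shows the effect.

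**5. Cut-off.** Above 16 (Abstract) rejects a score of 16. Exclusion below 16 (Study population, Sample size) accepts it.

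**The case against.** A reader might infer that the trial fails to deliver 46 per arm or 90% power. The article does not support that. On the Abstract's reading, 120 leaves 48 per arm at 20% drop-out, more than the plan asks for. On the less favourable reading, 43 per arm still gives about 91% at ρ = 0.5. Correlations low enough to produce a large shortfall, such as 0.4, conflict with the plan's simulation result, because 46 per arm would then give only 87.7%.

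A reader might also infer that ineligible people are randomised. This is not established. Sample size speaks of subjects in the study, Procedure has an investigator assess eligibility at a call-back, and the flow chart cited for the 120 is not shown and may place the exclusions. What stands is that the two statements about 120 disagree in the text.

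Third, 28% and 38% are treatment drop-out rates. A participant can stop the sessions and still complete the week 8 PSS-10; Procedure plans e-mail reminders and a call for late questionnaires, and Statistical analyses plans multiple imputation. The 20% is therefore unexplained beside the cited rates, not shown to be wrong.

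Finally, 3.6 against 3.45 is a matter of rounding, and the section presents its means as expected values for a more stressed population. This is minor.

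**Conclusion.** The point holds in a limited form. The inflation is additive and does not follow from the stated losses: if both fall on the 120, 43 per arm remain instead of 46, and 128 would be needed. The cost in power is about 2 percentage points: from 92.7% to 91.0% at ρ = 0.5, or from 90% to about 88% at the lowest compatible ρ of about 0.44. These powers assume SD 5, a two-sided 5% test and a difference of 3.6; ρ is an assumption. The arithmetic in steps 1 and 2 needs none of these.

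The contradictions over what 120 counts and over a score of 16 are plain in the text and must be reconciled. The drop-out assumption is an unexplained gap. Nothing here shows that 120 is too few if it means eligible, randomised participants and 20% loss is realistic for the week 8 PSS-10.

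**What to change.** Keep 120 and state what it counts.

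- **If it means eligible, randomised participants:** remove the 10% from the inflation and state 96 evaluable at 20% drop-out (48 per arm, about 94% at a difference of 3.6 and ρ = 0.5). Add a sensitivity line for higher loss: 28% leaves 43 per arm (about 91%), 38% leaves 37 per arm (about 86%).
- **If it includes people later excluded for a PSS-10 below 16:** state 86 evaluable (43 per arm) and the correspondingly lower power, and reconcile these exclusions with the intention-to-treat analysis.
- **Difference:** if 3.45 is adopted in place of 3.6, recompute the powers to match. At ρ = 0.5, 48, 43 and 37 per arm then give about 92%, 88.5% and 83%. Do not pair 3.45 with powers computed at 3.6.
- **Drop-out:** say in one sentence why 20% loss of the week 8 PSS-10 is expected, given the cited treatment drop-out.
- **Cut-off:** give one PSS-10 rule in the Abstract, Study population and Sample size, so that a score of 16 is handled one way.

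The cost is rewording one paragraph and aligning one criterion, with no extra participants. Trial status says that enrolment had not started, so this can be settled before the first inclusion.

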### Outcomes

#### Primary outcomes

The decrease of the Perceived Stress Scale – 10 items version (PSS-10) [30] score at 8 weeks will be our primary outcome. The 10 items of the PSS range from 0 (never) to 4 (very often); higher scores are indicative of higher perceived stress. The PSS-10 is validated in French [32], and its ease of use and psychometric properties have been widely studied in professional contexts [33]. The expected PSS-10 values are 23 ± 5 initially with a decrease to 19.6 (control group) and 16 (experimental group).

#### Secondary outcomes

The Patient Health Questionnaire – 2 items version (PHQ-2) [34] will be applied to screen for depression. Each item is scored on a scale ranging from 0 (not at all) to 3 (nearly every day).

The Short Form Posttraumatic Stress Disorder Checklist 5 (SF-PCL-5) [35] will be used to screen for post-traumatic stress symptoms. It consists of 4 items ranging from 0 (not at all) to 4 (extremely).

The Connor-Davidson Resilience Scale – 2 items version (CD-RISC 2) [36] will be used to measure resilience. The 2 items are scored on a scale ranging from 0 (not true at all) to 4 (almost always true).

A short form of the Insomnia Severity Index (ISI) [37] will be used to measure the severity of insomnia using 5 of the initial 7 items of the ISI. Each item is scored on a scale ranging from 0 (not at all) to 5 (extremely).

The Affective Rumination Questionnaire (ARQ) [38] will be applied to measure work-related rumination. The 5 items are rated on a scale ranging from 0 (very rarely or never) to 4 (very often or always).

Self-reported credibility of the treatment will be assessed via the Credibility and Expectancy Questionnaire (CEQ) [39] at baseline and at 8 weeks of treatment. This questionnaire contains 6 items rated either from 1 to 9 or from 0 to 100% and evaluates whether the participants “think” or “feel” that their treatment will be efficient.

Finally, the Client Satisfaction Questionnaire (CSQ-8) [40] will be applied as a self-report measure assessing participants’ satisfaction at the end of the 8-week program. The 8 items are scored on a scale ranging from 1 to 4. Higher scores are indicative of elevated satisfaction.

To measure the perceived efficacy and utility of each individual session of the CBT program, participants will complete visual analog scales (VAS) measuring stress, sleep, self-efficacy, and mood before each session; two VAS will be administered after each session to measure perceived stress and utility of the session.

The following measures will be used to assess acceptability: the number of participants having completed the program (i.e., ≥ 5/7 sessions) compared to the number of participants connected to the platform (number of drop-outs); the program completion time (from minimum 3 weeks to maximum 8 weeks); the utility of each session, assessed via the VAS after each session; how often the telephone hotline was used; and over the course of the 7 sessions, the relative ratings of perceived stress and self-efficacy and how often subjects practiced the skills associated with each session (Table 1).

